**Abstract/Summary:**

BACKGROUND: Palonosetron is a second generation serotonin antagonist usually used in a ﬁxed dose of 75 mcg for the prophylaxis of postoperative nausea and vomiting. Although there are a few trials evaluating bodyweight-adjusted doses of palonosetron, the ideal dose for obese patients has not yet been investigated. The aim of this study is to evaluate if the use of bodyweight-adjusted doses of palonosetron (1mcg / kg) is more effective than a fixed dose (75mcg) on preventing postoperative nausea and vomiting in female patients with a body mass index equal to or above 30 kg /m2 whom have undergone breast surgery

METHODS: A prospective, randomized double-blind trial will be conducted at the National Cancer Institute (INCA - HCIII), in Rio de Janeiro, Brazil. Eligible patients are female aged between 18-70 years of age with an ASA physical status of one to three, with body mass index equal to or greater than 30 kg / m2, scheduled to undergo elective breast surgery. Forty patients will be randomized to receive a bodyweight-adjusted dose of 1mcg/kg of palonosetron (group I - GI) and 40 patients will receive a fix dose of 75 μg of palonosetron (group II - GII). Patients will be assessed over 4 time periods: 0-1h, 1-6 h, 6-24 h and 24-48 h after surgery. After discharge, all patients will be contacted by telephone at regular intervals to record the episodes of nausea and vomiting as well as analgesic and antiemetic requirements. The primary outcome measure will include the number of emetic episodes, the incidence of nausea, the need for rescue antiemetics and the analgesic requirement over 48h. The secondary outcome will be to evaluate the frequency of polymorphism of the 5-HT3 receptors and their correlation with the antiemetic effect and adverse effects.

**Introduction**

Prevention of nausea and vomiting after surgery is a routine throughout anesthetic-surgical procedure, since the discomfort and morbidity associated with this anesthetic complication are widely known. The serotonin antagonists are largely used for this purpose because they exhibit superior prophylactic efficacy when compared with other antiemetic drugs. Its mechanism of action is the inhibition of calcium influx caused by stimulation of serotonin 5-hydroxytryptamine type 3 receptor (5-HT3).

Palonosetron is a second generation serotonin antagonist with high affinity binding to the 5-HT3 receptor. It has a unique chemical structure and longer half-life than older 5-HT3 antagonists. It was initially approved for use in the prevention of chemotherapy induced nausea and vomiting but also proved effective in the prophylaxis of postoperative nausea and vomiting. Palonosetron is usually used in a ﬁxed dose of 75 mcg for the prophylaxis of postoperative nausea and vomiting. Although there are a few trials evaluating bodyweight-adjusted doses of palonosetron, the ideal dose of obese patient has not yet been investigated.

**Aims & Objectives**

Our hypothesis for this study is that the use of bodyweight-adjusted doses of palonosetron (1mcg / kg) is more effective than a fixed dose (75mcg) for preventing postoperative nausea and vomiting in female patients with a body mass index equal to or above 30 kg / m2 whom have undergone breast surgery.

Primary objectives:

1. To determine the frequency of individual episodes of nausea in the periods of 1, 6, 24 and 48 hours postoperatively
2. To determine the frequency of individual episodes of vomiting in the periods of 1, 6, 24 and 48 hours postoperatively
3. Compare need of antiemetic rescue medication during the periods of 1, 6, 24 and 48 hours postoperatively
4. Determine the number of patients who had complete antiemetic response (absence of nausea, vomiting and need for rescue medication).

Secondary objectives: To evaluate the frequency of polymorphism of the 5-HT3 receptors and their correlation with the antiemetic effect and adverse effects

### Methods

A prospective, randomized double-blind trial will be conducted at the National Cancer Institute (INCA - HCIII), in Rio de Janeiro, Brazil. All patients will be provided with written informed consent form prior to study enrolment. Eligible patients are female aged between 18-70 years of age with an ASA physical status of one to three, with body mass index equal to or greater than 30 kg / m2, scheduled to undergo elective breast surgery. The exclusion criteria are: patients who had received chemotherapy within 4 weeks, patients who have undergone emergency surgery, with known history of vomiting within 24 hours; a known hypersensitivity to other 5-HTantagonists, patients who received any antiemetic, corticosteroid, or other drug with antiemetic effect, smokers and patients with a history of alcoholism.

Using computer-generated random numbers, the patients will be assigned into one of the two treatment groups on the morning of surgery. Forty patients will be randomized to receive a bodyweight-adjusted dose of 1mcg/kg of palonosetron (group I - GI) and another forty patients will receive a fix dose of 75 μg of palonosetron (group II - GII). Each study drug will be mixed with saline to a total volume of 10 ml in an unlabelled syringe and will be intravenously administered just prior to induction of anesthesia. All patients, surgeons, anesthesiologists involved in the study will be blinded to group allocation to maintain the double-blind conditions.

All patients will receive premedication with midazolam. Intraoperative monitoring included electrocardiography, blood pressure measurement, peripheral oxygen saturation (SpO2), and end-tidal CO2 tension (ETco2). General anesthesia was induced using 1,5 mg/kg of propofol, 3 μg/kg of fentanyl, 1,5 mg/kg of lidocaine and 0.3 mg/kg of rocuronium. Then the insertion of laryngeal mask will be performed and the pulmonary ventilation will be maintained with 6 ml/kg of ideal-weight and maximum peak pressure 25 cmH2O. The anesthesia will be maintained with sevoflurane in 50% oxygen/air. Sevoflurane concentration was adjusted to ensure an equal depth of anesthesia during surgery as assessed by the bispectral index (BIS; BIS A-1050 Monitor, Aspect Medical Systems, Newton, MA, USA), which will be held between 40-60. Remifentanil will be administered for supplemental intraoperative analgesia and its dose will be adjusted to maintain blood pressure and heart rate within 20% of baseline values. At the end of surgery, residual neuromuscular blockade will be reversed with 2mg/kg of Sugammadex and the laryngeal mask will be removed. Patients will stay on the postanesthetic care unit for at least 1 hour before going to the ward. In the postoperative recovery room, the haemodynamic variables along with postoperative complications such as shivering, hypotension, dizziness, constipation or any other adverse reaction to the drug will be recorded by a blinded observer. After surgery, rescue medication will be intravenous metoclopramide (10 mg) for more than one episodes of nausea or vomiting.

All episodes of nausea and vomiting will be recorded for 48h. Patients will be assessed over 3 time periods: 0-6 h, 6-26 h and 24-48 h after surgery. After discharge, all patients will be contacted by telephone at regular intervals to record the episodes of nausea and vomiting as well as analgesic and antiemetic requirements. The primary outcome measure will include the number of emetic episodes, the incidence of nausea, the need for rescue antiemetics and the analgesic requirement after 48h. Nausea is deﬁned as a subjective unpleasant sensation associated with the urge to vomit without expulsion of gastric content and vomiting is deﬁned as the forceful expulsion of gastric contents trough the mouth.

The secondary outcome will be to evaluate the frequency of polymorphism of the 5-HT3 receptors and their correlation with the antiemetic effect and adverse effects. The patients will have cell samples of the oral cavity, collected through smear. The collected material will be placed in a tube and then will be stored at freezer. Then, it will be analyzed in the laboratory of Clinical Research Unit at the Federal Fluminense University (UFF). After extracting the DNA from the samples using a DNA purification kit, a polymerase chain reaction (PCR) will be performed for analysis of single nucleotide polymorphisms. Biological samples will be discarded at the end of the analysis.

Sample size was calculated with reference to the results of a study comparing weight-adjusted doses of palonosetron for prevention of PONV in laparoscopic gynaecological surgery in no-obese patients. For a P value of 0.05 and a power of 0.8, a minimum of 36 per dose group was required. To allow for possible dropouts, the aim was to recruit 40 patients in each group.

GraphPad Prism 4.0® (GraphPad Softwares Inc., San Diego, CA, USA) will be used for statistical analysis. The Wilcoxon signed rank 2x2 test will be use to ensure that data will be normally distributed. Patient characteristics and intra- and post-operative variables will be analysed by Unpaired Student´s t-test. Proportions will be compared using x^2^ square or Fisher’s exact test. A P value < 0.05 is considered statistically significant.

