**Study Administration & Ethical Issues**

The study was approved by the Institutional Ethics Review Committee (Research Ethics Committee (CEP) of INCA), which is formed by professionals from different fields whom review research projects involving human subjects, to ensure the rights, safety and well-being of all volunteers who participate in these studies. Contact the CEP INCA, from Monday to Friday 9:00am to 5:00 pm, by the phones [contact] and also by e-mail: [contact].

Some adverse effects may occur with the use of medication, the most frequent being sedation, headache and dizziness. There are also the risks inherent to anesthetic-surgical procedures, such as infection, bleeding, arrhythmias, allergies and pain.
 The information about patient’s health and personal information will be kept private and confidential. The data will only be used anonymous (without identification). Only the authorized researchers will have access to individual´s data, results of examinations and tests as well as the information contained on the medical records. Even if this data is used for scientific publication, patient identification will remain secret. Any and all damages arising from the development of this research and in need of medical care is the responsibility of the institution.

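### The adverse effects named for recording do not match those the protocol calls most frequent: sedation and headache are left to a catch-all that turns on a causal judgement

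*Protocol*

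**What the plan says.** The Methods section of the Protocol has one sentence on how adverse effects are collected. It is set in the recovery room ("In the postoperative recovery room, the haemodynamic variables along with postoperative complications") and provides that "postoperative complications such as shivering, hypotension, dizziness, constipation or any other adverse reaction to the drug will be recorded by a blinded observer".

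The section Study Administration & Ethical Issues states what is expected: "Some adverse effects may occur with the use of medication, the most frequent being sedation, headache and dizziness". Its next sentence lists the risks of anaesthesia and surgery separately.

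The data have a stated use. The secondary outcome is the frequency of 5-HT3 receptor polymorphism and its "correlation with the antiemetic effect and adverse effects".

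The telephone follow-up is described by other content. Patients are "contacted by telephone at regular intervals to record the episodes of nausea and vomiting as well as analgesic and antiemetic requirements", and adverse effects are not mentioned there.

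**The concern.** The events a protocol names for collection should include those it expects most often. Here they largely do not. Two of the three effects ranked as most frequent are unnamed, and the wording that would take them in refers to reactions to the drug. Read literally, an unnamed event has to be attributed to palonosetron before it is recorded.

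That attribution is difficult in this setting. Every patient also receives midazolam, propofol, fentanyl, sevoflurane and remifentanil. Drowsiness in recovery has several possible causes, and an observer who does not know the allocation has little to separate them with. Whether sedation or headache is written down could then depend on the observer's habit and not on a rule.

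Two uses of the data are exposed. One is the secondary outcome, which needs adverse effects recorded consistently across genotypes. The other is any tolerability comparison between arms. Group I receives 1 mcg/kg, so a woman above 75 kg gets more than the fixed 75 mcg (1 mcg/kg × 75 kg = 75 mcg), and readers will look for such a comparison. An event that was never recorded cannot be recovered in the analysis.

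**Working it through.** **Side-by-side check**

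| Effect | Named for recording (Methods) | Called most frequent (Study Administration & Ethical Issues) |
|---|---|---|
| Dizziness | yes | yes |
| Sedation | no | yes |
| Headache | no | yes |
| Shivering | yes | no |
| Hypotension | yes | no |
| Constipation | yes | no |

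The overlap is 1 of 3, so 2 of 3 of the most frequent effects are not named.

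**How the Methods sentence treats an unnamed event**

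1. The list opens with *such as*, so the four named events are examples. Sedation and headache are not ruled out.
2. The list closes with a residual category, and that category alone carries a condition: a reaction to the drug. The four named events carry none.
3. An unnamed symptom could therefore be recorded as one more postoperative complication, without attribution, or held to the drug-reaction condition. The sentence does not say which. Two observers could follow it in good faith and record differently.

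**Can the effect be sized?** Not from the documents, which give no adverse-effect rates and nothing on completeness of recording. The following is an illustration on assumed values only.

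- Assumed true rates: 40% v 20%. Arm size from the Protocol: 40 per group.
- Assumed share of events recorded, equal in both arms: c = 100%, 50% or 25%.
- Recorded rate = c × true rate, so recorded difference = c × (0.40 − 0.20). The ratio stays at 2.
- Test: two-sided Fisher's exact test at 0.05. Power is the sum of the binomial probabilities of all tables with p < 0.05.

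| c | Recorded rates | Expected counts of 40 | Recorded difference | Fisher p at those counts | Power |
|---|---|---|---|---|---|
| 100% | 40% v 20% | 16 v 8 | 20 points | 0.087 | 41% |
| 50% | 20% v 10% | 8 v 4 | 10 points | 0.35 | 16% |
| 25% | 10% v 5% | 4 v 2 | 5 points | 0.68 | 4% |

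Equal loss in both arms leaves the ratio alone, shrinks the absolute difference and lowers power. The first row also shows that 40 per arm is weak for such a comparison even when every event is recorded.

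**The case against.** The case against giving this much weight is strong, and most of it stands.

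- **Nothing is excluded.** The list is illustrative and open, and the Protocol itself classes sedation and headache as effects of medication, so they fit the residual category. This stands. The defect is that they are not named and that the category is conditional.
- **The sentence may not be the working checklist.** It is narrative text, and a case report form, which is not shown, could name these items. This stands as a possibility. But a form written to follow the sentence would carry the same gap.
- **Nothing says symptoms must be volunteered.** This is correct. The text says an observer records them and is silent on whether patients are asked. Sedation is in any case a sign that an observer can see.
- **The observer is blinded.** This stands. Any loss should fall on both arms about equally, so there is no reason to expect it to favour one of them. Lost precision remains.
- **The illustration does not isolate the wording as the cause.** This stands. With full recording, 16 v 8 of 40 already gives p = 0.087, so the size of the trial is the main limit on any safety comparison.
- **Safety is not a stated between-arm objective.** This is correct. Aims & Objectives brings in adverse effects only through the polymorphism objective.

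A reader might go further and infer that the main effects of palonosetron will be under-counted, and that a finding of no difference would be an artefact of this. The documents do not support that. They show a risk of uneven recording, give no rates, and speak of *medication* without naming palonosetron. The separate listing of anaesthetic and surgical risks makes the study drug the natural reading, but that is still an inference.

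**Conclusion.** The point holds as a minor one. The two sections list different effects, and two of the three called most frequent depend on a residual category whose condition a blinded observer cannot reliably apply after midazolam, opioids and general anaesthesia. The consequence is a risk of inconsistent or incomplete recording of sedation and headache, probably similar in both arms. It would cost precision in the genotype and adverse-effect outcome and in any comparison of tolerability.

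The size cannot be stated, since the tabulated powers and p-values rest wholly on assumed rates and capture. The conclusion assumes that the Methods sentence governs what is collected and that no unseen form already names these items. It concerns which events are recorded and on what condition. How long adverse effects are followed is a separate matter.

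**What to change.** 1. Align the Methods list with the ethics section, so that headache, sedation and dizziness are each recorded as a named item, present or absent, for every patient. Keep the events already listed.
2. Replace the closing category with *any other adverse event, regardless of presumed cause*. Judge cause in a separate field while still blinded.
3. Compare arms on all recorded events. Randomisation should balance the anaesthetic background on average, so filtering by cause is not needed for a fair comparison.

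The cost is two further items on the observer's form and a change of wording. The drawback is a higher and noisier raw count, because anaesthetic effects will be included. The separate judgement of cause lets them be set apart when results are reported.

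### The only adverse-effect collection the protocol states is in the recovery room, so the genotype–adverse-effect objective lacks a stated source of data for most of the 48 h follow-up

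*Protocol*

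**What the plan says.** In the Protocol's Methods, the sentence on adverse reactions opens by naming the postoperative recovery room as the setting. It then says that "complications such as shivering, hypotension, dizziness, constipation or any other adverse reaction to the drug will be recorded by a blinded observer". The length of stay there is given as a minimum: "Patients will stay on the postanesthetic care unit for at least 1 hour before going to the ward".

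For the rest of follow-up the Methods state what is captured. "All episodes of nausea and vomiting will be recorded for 48h", and after discharge patients are telephoned "to record the episodes of nausea and vomiting as well as analgesic and antiemetic requirements". The Abstract gives the same telephone list.

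Adverse effects are nevertheless part of a stated objective. Under Aims & Objectives the secondary objective is: "To evaluate the frequency of polymorphism of the 5-HT3 receptors and their correlation with the antiemetic effect and adverse effects". The Abstract and the Methods repeat it. None of the three gives a time window for the adverse effects.

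Study Administration & Ethical Issues says what is expected: "Some adverse effects may occur with the use of medication, the most frequent being sedation, headache and dizziness".

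**The concern.** The secondary objective has two halves. The antiemetic half has a 48 h record. The adverse-effect half has only a stated recovery-room record, and the explicit content lists for later contacts leave adverse effects out.

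Three things are at stake. First, effects that appear on the ward or at home have no stated route into the data. Secondly, the effects that can be seen in the recovery room are hard to attribute. These patients have just received midazolam, fentanyl, remifentanil and sevoflurane, so sedation, dizziness, shivering or hypotension at that point may owe little to the study drug or to receptor genotype. Thirdly, the trial has about 80 patients, so losing later events leaves few to set against genotype. No analysis plan can recover data that were never collected.

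**Working it through.** The protocol gives no figure to reproduce on this point. The check sets the statements side by side, computes the stated window as a share of follow-up, and then shows what incomplete capture does to a correlation.

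**1. What is collected, where and when**

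| Statement | Setting or period | Adverse effects included? |
|---|---|---|
| Methods: "In the postoperative recovery room, the haemodynamic variables along with postoperative complications such as shivering, hypotension, dizziness, constipation or any other adverse reaction" | Recovery room, at least 1 h | Yes |
| Methods: 48 h recording sentence | 0–48 h | No: nausea and vomiting only |
| Methods and Abstract: "contacted by telephone at regular intervals to record the episodes of nausea and vomiting as well as analgesic and antiemetic requirements" | After discharge | No |
| Methods and Abstract: assessment periods | To 48 h | Content not specified |
| Ward stay between recovery room and discharge | Not described | Not described |

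One row includes adverse effects, two list other content, and two are silent.

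**2. Window as a share of follow-up**

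Share = recovery-room hours / 48.

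- Stated minimum, 1 h: 1/48 = 2.1%
- Assumed 2 h: 2/48 = 4.2%
- Assumed 3 h: 3/48 = 6.3%
- Assumed 6 h: 6/48 = 12.5%

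Even at 6 h, 100% − 12.5% = 87.5% of the follow-up has no stated adverse-effect collection. These are shares of time, not of events.

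**3. Effect on the genotype analysis (illustration)**

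Assume a true 48 h incidence p for some effect and a captured fraction c that is the same in every genotype group, with no false positives. The protocol gives neither value; p = 20% and c = 100%, 50% and 25% are assumptions. With all 80 recruited patients, expected events are 80 × p × c:

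- c = 100%: 80 × 0.20 × 1 = 16
- c = 50%: 80 × 0.20 × 0.50 = 8
- c = 25%: 80 × 0.20 × 0.25 = 4

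Between two genotype groups the risk ratio is unchanged, because (c·p1)/(c·p0) = p1/p0. The risk difference becomes c·(p1 − p0). The phi correlation is multiplied by √[c(1 − p)/(1 − cp)]:

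- c = 50%: √(0.50 × 0.80/0.90) = 0.67
- c = 25%: √(0.25 × 0.80/0.95) = 0.46

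Under equal capture, then, precision falls on every scale, while attenuation depends on the scale. If capture differs by genotype, the direction is not determined.

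**4. Fit of the listed items to the setting**

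Constipation is named for recording in a place where the stated minimum stay is 1 h. Whether it can be observed there is a matter of judgement rather than of calculation, but a stay of that length can hardly show it.

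**The case against.** The strongest reply is that the gap is inferred from silence. Nothing forbids later recording, and the assessment periods run to 48 h without saying what is assessed. Constipation in the list may even mean that the authors intended later recording and worded the sentence loosely. This stands in part: the protocol does not say that adverse effects will go unrecorded after the recovery room. It does say what the telephone contacts are for and what is recorded for 48 h, and adverse effects are in neither list. Staff following it as written would have no instruction to ask. If later recording was intended, the text needs the same correction.

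A reader might infer several stronger claims that the document does not support:

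- That observation is limited to about the first hour. One hour is a minimum with no stated maximum.
- That headache and sedation are left out. They are not named in the Methods list, but its catch-all for other adverse reactions covers them.
- That the trial's safety comparison between arms fails. No such comparison is a stated objective; adverse effects enter only through the genotype correlation.
- That results would necessarily be biased towards no association. The ratio scale need not be affected, and the protocol gives no event timing from which to judge.
- That the drug's half-life shows there will be late effects. The Introduction says only that it is longer than that of older agents in the class, and links this to no adverse effect.

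**Conclusion.** The point holds in this form: the protocol states adverse-effect collection only in the recovery room, while its secondary objective needs adverse-effect data and gives no window for them. As written, the objective rests on a stated minimum of 1 h out of 48 h (2.1%), or up to 12.5% if stays of 6 h are assumed. Drug effects in that window are mixed with recovery from anaesthesia, and one listed item can hardly be observed.

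The consequence is fewer events and a less precise, possibly attenuated, correlation with genotype. How many events would be missed is unknown. The conclusion assumes that staff collect what the protocol lists and no more.

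The matter should be corrected because a stated objective depends on it and later analysis cannot repair it. The stated recording of nausea, vomiting and rescue antiemetics is not touched by it.

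**What to change.** Add a fixed adverse-effect checklist to the assessments and telephone contacts already planned to 48 h, including the ward. It should name headache, sedation and dizziness, which the protocol expects to be most frequent, together with constipation, shivering and hypotension, and keep an open item for anything else. Record the period in which each effect is reported, so that recovery-room effects can be told apart from later ones.

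State in the Methods that the 0–48 h record supplies the adverse effects for the genotype analysis. The Abstract and the Methods list different assessment periods; settle these at the same time so that the checklist has one timetable.

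The cost is a few more questions at contacts already scheduled and a change to the case report form and telephone script. It adds no patients and no visits. A descriptive tabulation of adverse effects by arm could be made from the same record, but it is optional and not part of the error.

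### The Methods assess three overlapping windows with no cut at 1 h, whereas the abstract uses four and three primary objectives require 1 h, so the by-period primary results are undefined

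*Protocol*

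**What the plan says.** The protocol describes the timing of outcome assessment in three places.

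- **Methods (outcome assessment paragraph):** "Patients will be assessed over 3 time periods: 0-6 h, 6-26 h and 24-48 h after surgery".
- **Abstract/Summary:** "Patients will be assessed over 4 time periods: 0-1h, 1-6 h, 6-24 h and 24-48 h after surgery".
- **Aims & Objectives:** objective 1 is "To determine the frequency of individual episodes of nausea in the periods of 1, 6, 24 and 48 hours postoperatively", objective 2 is "To determine the frequency of individual episodes of vomiting in the periods of 1, 6, 24 and 48 hours postoperatively" and objective 3 is "Compare need of antiemetic rescue medication during the periods of 1, 6, 24 and 48 hours postoperatively". Objective 4, complete response, names no period.

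Two further statements in the Methods bear on what will be captured. Immediately before the three-window sentence comes "All episodes of nausea and vomiting will be recorded for 48h". Immediately after it comes "After discharge, all patients will be contacted by telephone at regular intervals to record the episodes of nausea and vomiting", and that sentence goes on to include analgesic and antiemetic use. The protocol does not say whether the clock time of an episode or of a rescue dose is written down.

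**The concern.** The Methods paragraph is the one that staff would follow at the bedside and by telephone, and it differs from the other two places in the number of windows and in their bounds. Three of the four primary objectives are stated by period, so the conflict lies in the definition of primary results.

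If the forms and calls follow the Methods wording and record only the window in which an event occurred, the first postoperative hour cannot be separated from the next five. A later analysis plan cannot restore a cut that was not collected. The literal 6-26 h window also assigns events at 24-26 h to two periods.

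**Working it through.** **Inputs.** The window bounds come from the Methods and the abstract. The required time points come from primary objectives 1 to 3.

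**Formulas.** Length of a window = end − start. Overlap of consecutive windows = max(0, end of the earlier − start of the later).

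**Methods windows as written (0-6, 6-26, 24-48 h).**
- Lengths: 6 + 20 + 24 = 50 h, within a 48 h follow-up.
- Overlaps: max(0, 6 − 6) = 0 h and max(0, 26 − 24) = 2 h.
- 50 − 2 = 48 h, so there is no gap. The excess is entirely the stretch from 24 to 26 h.

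**Methods windows with 26 read as 24 (0-6, 6-24, 24-48 h).**
- Lengths: 6 + 18 + 24 = 48 h, overlap 0 h.

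**Abstract windows (0-1, 1-6, 6-24, 24-48 h).**
- Lengths: 1 + 5 + 18 + 24 = 48 h, overlaps 0, 0 and 0 h.

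**Comparison with the objectives (1, 6, 24, 48 h).**

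| Schedule | Windows | Total length | Overlap | Boundary at 1 h? | Clean boundary at 24 h? |
|---|---|---|---|---|---|
| Methods, as written | 3 | 50 h | 2 h | No | No |
| Methods, 26 read as 24 | 3 | 48 h | 0 h | No | Yes |
| Abstract | 4 | 48 h | 0 h | Yes | Yes |

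The objectives' wording could mean separate periods (0-1, 1-6, 6-24, 24-48 h) or cumulative ones (0-1, 0-6, 0-24, 0-48 h). Both need boundaries at 1, 6, 24 and 48 h, so the result does not depend on which was meant.

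**Consequence if only the window is recorded.** The 1 h result is missing for three outcomes: nausea, vomiting and rescue. If separate periods were meant, the 1-6 h result is missing too. Under the literal wording, window counts alone also give no clean 6-24 h result.

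**Effect on 48 h results.** Let x be the number of episodes at 24-26 h. Adding the three window counts gives the true 48 h total + x. A total taken directly from the 48 h record has no such excess. The documents give no basis for estimating x. Complete response is a yes/no status per patient; if it is judged over the whole follow-up, it needs no internal cut and does not change when an event is listed in two windows.

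**The case against.** The strongest reply is that the by-period results may be fully recoverable. The Methods have every nausea and vomiting episode recorded over 48 h, and patients remain in the recovery unit for no less than 1 h, which puts observers in place for the first window. If each episode carries a time, any set of windows can be built afterwards. This stands in part. The protocol neither states nor excludes that times are noted, so a reader who infers that the 1 h results are certainly lost goes further than the text allows. The reply is weaker for rescue, because the sentence on complete recording names only nausea and vomiting. Recording of antiemetic use is mentioned only for telephone contacts after discharge.

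A second reply is that 6-26 is a typing slip for 6-24. That is likely: the next window starts at 24 h, and the abstract and objectives both use 24 h. It removes the overlap, but the sentence would still announce and list three periods, with no cut at 1 h.

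A third reply is that the primary outcome paragraph is framed on a 48 h horizon and that only objective 3 speaks of comparing. Both observations are correct and limit the reach of the point. They do not remove objectives 1 to 3, which are listed as primary and name 1 h.

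**Conclusion.** The Methods contradict the abstract and primary objectives 1 to 3 on the number and bounds of the assessment windows, which leaves the by-period primary results undefined. The size is one missing boundary (1 h), affecting three of the four primary objectives, and one 2 h overlap (24-26 h) that is probably a slip.

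The unavailability of the 1 h results is conditional: it follows if data are captured only by the Methods windows. Three stronger readings are not supported:

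- **The by-period primary results cannot be produced at all.** The 48 h record of episodes could supply them if times are noted.
- **Events at 24-26 h will be counted twice in 48 h totals.** This requires totals to be built by adding window counts, which the protocol does not describe.
- **The choice of periods is left open until the data are seen.** A statistical analysis plan may exist and may settle this; it is not shown.

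Complete response and 48 h totals stand, provided that each 24-26 h event is counted once. No sample-size figure is affected.

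**What to change.** Replace the three-window sentence in the Methods with the abstract's four windows, written so that they do not overlap: 0-1, >1-6, >6-24 and >24-48 h. Add a sentence saying that the time of each nausea or vomiting episode and of each rescue dose is recorded, from the recovery unit through the telephone contacts, so that every event falls in exactly one window.

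The cost is two sentences of protocol text, plus a check that the data collection form and telephone script (neither is shown) follow the same windows. The first-hour assessment fits the minimum recovery-unit stay already planned. The sample size does not change. The correction should be made before data collection starts, because a boundary that is not recorded may not be recoverable later.
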